**Abstract**

**Background:** Remote access to health care optimizes the use of local resources, facilitates access to care and minimizes the risk of covid-19 contagion. This study aims to describe indicators of feasibility including patient recruitment, attendance, discomfort, satisfaction and travel time and cost savings of virtual telemedicine consultations for patients with dementia. **Methods:** Virtual telemedicine consultation with patients and their caregivers will be similar to a routine face-to-face consultation. We will perform a single-center one-arm study with indicators of feasibility as the study primary endpoints.

**Ethics and dissemination:** The study is approved by the Research Ethics Committee of Hospital Universitário Walter Cantidio and all participants will provide their written informed consent (register number 31779920.1.0000.5045).

Trial results will be disseminated via peer reviewed journal articles and conference presentations, reports for organisations involved with PD and for participants. Trial registration number Registro Brasileiro de Ensaios Clínicos Registry (RBR-9xs978).

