We will use the AMT-4 to assess cognitive function. Brief cognitive tests such as the AMT-4 and AMT-10 have been widely used in acute care units of UK hospitals and shown good sensitivity for detecting delirium as well as previously diagnosed dementia.^17^ The AMT-10 was not superior to the AMT-4 in a validation study conducted in Brazil.^18^ The cut-off points of three or more correct answers (AMT-4) showed an even higher sensitivity (80%) than the ten-item test, with good specificity (88%) and good reliability^19^. The four questions that will be asked are: 1 – current time (correct answer: ±1 hour); 2 – home address instead of hospital name as the patients were at home; 3 – date of birth; 4 – counting backwards by 1 from 20 to 1.

The Katz scale is widely used to assess activities of daily living (ADLs) rated on a scale of 0 to 6. It has been developed as a predictor of treatment outcomes in older people and patients with chronic conditions. This 6-item scale grades performance on self-care activities following a hierarchy of complexity: feeding; continence; transferring; personal hygiene; dressing; and bathing. Independence means being able to perform these activities without supervision, guidance or active personal assistance. The assessment is based on actual performance, not skills. Those refusing to perform an activity are considered dependent, even though they are believed to be capable of doing it. We administered a version of the Katz scale that was translated and culturally adapted to Brazilian Portuguese by Lino et al. (2008), where higher scores indicate more dependence.^20^

Primary outcome measures

*Recruitment rate*

Eligible patients will be asked to sign an informed consent form and an appointment will be scheduled using WhatsApp messenger or via telephone. They will receive some instructions to optimize the remote consultation: choose an adequate room with strong wi-fi signal; have their caregiver or a family member present during the entire appointment; and have their most recent test results and list of medications at hand.

The recruitment rate for telemedicine consultations will be calculated by the number of patients agreeing to participate in the study divided by total number of patients which we will have attempted to contact.

*Attendance*

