The attendance rate will be calculated by the proportion of virtual medical consultations completed as scheduled. The intervention will be considered feasible if at least 80% of the consultations could be completed.^21^

*Acceptance*

A self-administered questionnaire will be used to evaluate whether our telemedicine intervention is feasible, safe, satisfying and well-accepted for future use. This questionnaire will be answered with the help of the caregiver for patients with early dementia and by the caregivers themselves for patients with moderate to severe dementia. They will be asked to inform the questionnaire’s respondent. The questionnaire consists of 12 questions with a visual analogue scale (VAS) to evaluate satisfaction (worst on the left end and best on the right end) and one additional open-ended question. The participants will be asked to mark the point (face) on a horizontal line that is representative of their level of satisfaction. For each question, they can select only one option.

The questionnaire has five domains: feasibility (items 1–2); sense of safety (items 3–5); appreciation and satisfaction (items 6–7); effectiveness (items 8–9); acceptance and future use of the intervention (items 10–12). Lower scores indicate lower perceived interest, safety, satisfaction, acceptance and benefits of telemedicine. We also include an open-ended question for suggestions and comments. The VAS scale will be sent on WhatsApp as a Google Drive link. This same questionnaire has been administered by other authors^22,23^. If the participants do not complete the questionnaire within 45 days, it will be administered through a phone interview with the participants’ caregivers.

*Discomfort*

Patient discomfort during consultation will be assessed by the number of consultations with internet connection issues and/or the interviewer’s perception of patient behavior changes divided by the number of consultations.

*Travel time and cost savings*

Information on travel time and costs will be collected during the interview to capture both time and financial burden of face-to-face consultations. They will be asked about transportation, average travel time from the clinic to their home, and travel expenses.

*Statistical analysis*

For numerical variables, data will be presented as means, standard deviations and medians. For categorical variables, data will be described as frequencies.

Data Collection Methods

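### Discomfort, a descriptive primary outcome, counts a connection fault with a calm patient as patient discomfort, so the pooled rate is only an upper bound on distress

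*Protocol*

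**What the plan says.** The definition is in the Protocol, Methods/Trial design, in the Discomfort paragraph under the heading "Primary outcome measures". It begins "Patient discomfort during consultation will be assessed by the number of consultations with internet connection issues and/or". The alternative event that follows is one judged by the interviewer, and the sentence ends "perception of patient behavior changes divided by the number of consultations".

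The Abstract confirms the status of the outcome. It lists "indicators of feasibility including patient recruitment, attendance, discomfort, satisfaction and travel time and cost savings" and then makes "indicators of feasibility as the study primary endpoints". The feasibility lists in Background and rationale and in Study design leave discomfort out, but neither redefines it or removes it from the primary outcomes.

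For analysis, the Statistical analysis paragraph says "For categorical variables, data will be described as frequencies". It does not say that the two components of discomfort will be reported separately. The one numerical feasibility criterion is in the Attendance paragraph: "The intervention will be considered feasible if at least 80% of the consultations could be completed". Discomfort has no threshold.

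**The concern.** The numerator joins two different kinds of event. One is technical: the connection was faulty. The other concerns the patient: the interviewer saw a change in behaviour. Because either is enough, a calm patient whose video briefly froze counts the same as a patient who became agitated.

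The two events call for different responses. Connection faults point to better connectivity or support. Behaviour change raises the question of whether video suits some patients with dementia. A single figure under the name of patient discomfort does not tell the reader which problem was found.

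This matters because the behavioural observation has no substitute among the primary outcomes. According to the Acceptance paragraph, caregivers answer the questionnaire themselves when dementia is moderate to severe. The interviewer's observation is then the only primary outcome that directly records how such a patient reacted.

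**Working it through.** The protocol gives no expected discomfort rate and no rate for either component, so there is no figure to reproduce. The check is of the definition.

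**Step 1: classify each type of consultation under the stated rule.**

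| Connection fault | Behaviour change | Counted as discomfort? | Sign of patient distress? |
|---|---|---|---|
| no | no | no | no |
| no | yes | yes | yes |
| yes | yes | yes | yes |
| yes | no | **yes** | **no** |

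The rule and its label disagree in the last row, and every fault-only consultation falls there.

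**Step 2: bounds, with no assumption about dependence.** Let I be the share of consultations with a connection fault, B the share with perceived behaviour change, and C the pooled rate. Then max(I, B) ≤ C ≤ min(1, I + B). It follows that B ≤ C always, so C is an upper bound on the behaviour-change rate. C alone gives no lower bound above zero. A reported C of 20% fits B = 0% (every counted consultation was fault-only) and B = 20% (none was), and anything between.

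**Step 3: illustration with assumed rates.** Take B = 5% and assume the components are independent, so C = 1 − (1 − I)(1 − B). The fault-only share of the counted consultations is (C − B)/C.

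| Assumed I | C | Fault-only share of C |
|---|---|---|
| 0% | 1 − 1.00 × 0.95 = 5.0% | 0% |
| 5% | 1 − 0.95 × 0.95 = 9.8% | 49% |
| 10% | 1 − 0.90 × 0.95 = 14.5% | 66% |
| 20% | 1 − 0.80 × 0.95 = 24.0% | 79% |
| 40% | 1 − 0.60 × 0.95 = 43.0% | 88% |

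Counting behaviour change alone gives 5% in every row.

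**Step 4: effect on the feasibility decision.** The 80% criterion is stated for completed consultations and does not use C. It is unchanged whatever the value of C.

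**The case against.** Most of the case on the other side concerns how much follows from the defect, and much of it stands.

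- **A reader might infer that the rate cannot be interpreted at all.** The protocol does not support that. Behaviour change is inside the numerator, so a very low pooled rate would show that distress was rare. The figure can also be read as the share of consultations with any disturbance. What fails is reading a moderate or high value as the frequency of patient discomfort.
- **A reader might infer that connection faults will be the commoner component and will drive the rate.** The protocol gives no rate for either. It excludes patients without the necessary technology and asks participants for a good signal, which should reduce faults. It also excludes patients uneasy with virtual consultations, which should reduce behaviour change. The text does not settle which is commoner. Any multiple of the behavioural rate reflects the rates assumed: I = 20% with B = 10% gives 28%/10% = 2.8, while I = 40% with B = 3% gives 41.8%/3% = 13.9.
- **A reader might infer that consultations abandoned because of the connection drop out of the denominator.** The stated denominator is the number of consultations, with no restriction to completed ones. The Attendance paragraph, by contrast, explicitly counts completed consultations. The plain reading keeps abandoned consultations in.
- **The components may already be recorded separately.** The data form is not shown, and a statistical analysis plan, also not at hand, could add component frequencies. This is a fair limit on the consequences. It does not answer the point, because the protocol itself states the formula and the label, and the formula misclassifies every fault-only consultation.
- **No decision depends on the outcome.** This is correct. Discomfort has no threshold, test or role in sample size.

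**Conclusion.** The definition should be corrected, as a lesser point and not as a threat to the study's main conclusion. Applied as written, it reports an upper bound on perceived behaviour change under the name of patient discomfort. That conclusion rests on the wording alone and needs no assumed rates.

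The size does depend on assumptions. With 5% behaviour change, independent components and faults in 0% to 40% of consultations, the labelled rate is 5% to 43%. Without independence, a labelled rate of 20% fits any behaviour-change rate from 0% to 20%. A reader might infer that the feasibility conclusion is compromised; it is not, because the completion criterion does not use this outcome.

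**What to change.** Change the Discomfort definition so that the two components are recorded separately at each consultation and reported over one denominator, all consultations started:

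- (a) connection issues, as a technical-problem rate;
- (b) interviewer-perceived behaviour change, as the discomfort rate;
- the overlap, meaning consultations with both.

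Give counts with the proportions. The composite may be kept under a name such as any disturbance, but should not be labelled patient discomfort.

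The cost is one changed sentence in the protocol and, if they are not already there, two fields on the form. No extra visits or staff are needed. The price is that the reported discomfort rate rests on fewer events than the pooled rate and is therefore estimated from sparser data. The separate recording needs to be in place when each consultation takes place: if only the pooled item is captured, the split cannot be recovered from it later.

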## Baseline assessment

Allocation

Received virtual consultation

## Post-intervention Satisfaction

## Survey

Lost to follow-up

